## Abstract

**Background:**

University students face increasing academic, developmental, and psychosocial demands that place them at risk of reduced psychological well-being. Although positive psychology interventions have shown promising effects in this population, accessibility to them is limited. This barrier can be overcome by employing new technologies. However, none of the existing interventions that used ICT in this population was based on Seligman´s PERMA model, and they report low adherence rates. Complementing mobile-based interventions with brief telephone support may improve engagement and enhance outcomes. This study aims to evaluate the efficacy of a positive psychology–based psychological intervention grounded in the PERMA model delivered via a smartphone app, incorporating cognitive-behavioral self-regulation strategies (e.g., goal setting, self-monitoring, behavioral activation), with or without telephone multiconference support.

**Methods:**

A three-arm randomized controlled trial will be conducted with 177 university students, who will be assigned to: (a) an app-based PERMA intervention (PPIA), (b) the same intervention supplemented with weekly 30-minute telephone multiconference sessions (PPIA+M), or (c) a waiting list control group (WLCG). The intervention consists of five weekly modules targeting Positive Emotion, Engagement, Relationships, Meaning, and Accomplishment. Assessments will be conducted at baseline, post-intervention, and six-month follow-up. The primary outcome will be psychological well-being, measured with the Warwick–Edinburgh Mental Well-Being Scale (WEMWBS) and the Mental Health Continuum–Short Form (MHC-SF). Secondary outcomes include positive emotion, engagement, relationships, meaning, accomplishment, adherence, and satisfaction. Evaluations will be administered by independent, blinded assessors.

**Discussion:**

This study will provide evidence on the efficacy and acceptability of a brief PERMA-based digital intervention for university students. If effective, the program may represent a scalable and cost-efficient tool for promoting psychological well-being in higher education settings.

**Study Protocol Registration:**

ClinicalTrials.gov, identifier (NCT07466004).

## Introduction

1

Young adulthood, which generally spans from late teenage years to the mid-20s, represents a crucial period in people´s lives, marked by significant transitions that shape their future (1–3). During this phase, young adults face various challenges, such as pursuing higher education, establishing independence, forming intimate relationships, and making career decisions (4). These tasks are crucial for acquiring autonomy, exploring personal identity, and finding purpose, all of which are key elements of positive youth development (5, 6). Furthermore, the phase of young adulthood is characterized by individuals progressively assuming adult responsibilities, such as achieving financial autonomy, developing personal values, and taking charge of their health and wellness (7). Accomplishing these developmental tasks contributes to overall well-being, laying the foundation for future academic and career achievements, fulfilling relationships, and overall life satisfaction. Within the broader tapestry of society, university students emerge as a particularly significant demographic (8). They are not merely a subset of the population; they form a considerable proportion of their age group (9). In addition to these evolutionary achievements, university students face multiple academic and psychosocial demands that can deteriorate their psychological well-being and place them at risk for negative consequences on their mental health and academic functioning (10). The high prevalence of mental health problems such as anxiety and depression among university students has been well-documented in the literature (11, 12). These problems are associated with decreased academic performance, lower retention rates, and increased risk of dropout (13).

For all these reasons, the promotion of mental health in this population sector acquires vital relevance. Research findings confirm that prioritizing positive mental health enhances academic performance (14). Additionally, positive psychological well-being correlates strongly with improved interpersonal relationships and social integration within the university community. Students who manifest a state of positive mental health are characterized by robust communication abilities, elevated self-regard, and amplified empathetic responses; this constellation of attributes culminates in the cultivation of more fulfilling interpersonal connections with their contemporaries, academic personnel, and administrative staff (15). Furthermore, maintaining a positive state of mental health is essential for overall well-being and life quality; individuals who experience good mental health often report increased levels of life satisfaction, a heightened sense of purpose, and greater overall happiness (16, 17).

In recent times, the significance and recognition of mental health promotion have notably increased, especially as a crucial method to bolster the mental and emotional health of university students. As outlined by the National Research Council & Institute of Medicine (18), it involves strategies aimed at improving developmental competencies, self-esteem, mastery, well-being, and social inclusivity, while also enhancing resilience against challenges. It prioritizes empowering individuals and shaping environments that nurture mental health, going beyond merely addressing mental illness. The approach integrates proactive steps to fortify protective factors and foster positive mental health outcomes. It comprehensively considers the intricate aspects of psychological well-being, influenced by diverse social, cultural, and environmental elements. By leveraging techniques that underscore strengths, resilience, and affirmative relationships, it seeks to bolster both personal and communal resources, ultimately aspiring to elevate mental health and overall life quality (19).

Over the past several years, several studies have applied Seligman’s PERMA model (20)—which includes Positive Emotion, Engagement, Relationships, Meaning, and Accomplishment—in university contexts to enhance psychological well-being. The interventions based on this theoretical approach emphasize building students’ strengths and emotional resources through practical, reflective activities tied to everyday experiences. Among them, Sedeh and Aghaei (21) conducted a six-session program for university students in Iran, with each session focusing on one PERMA component. Activities included gratitude journaling, exploring personal strengths, group discussions, values clarification, and goal planning, resulting in significant improvements in psychological well-being. Similarly, Yang et al. (22) implemented a PERMA-based intervention with vocational nursing students in China to reduce social interaction anxiety and enhance subjective well-being. The program included mindfulness practice, journaling, empathy-building tasks, and goal tracking, and showed notable improvements in both emotional and social functioning. In a language learning context, Rogers et al. (23) integrated PERMA principles into English instruction. Weekly sessions featured activities like “three good things” journaling, peer appreciation, and reflections on meaningful experiences. Students reported increased engagement and connection, suggesting that PERMA-based activities can effectively enhance classroom dynamics. Finally, Ly and Nguyen (24) introduced PERMA-informed lessons in English-speaking classes, using storytelling, emotional vocabulary exercises, and reflective journaling, which helped students improve both language performance and emotional awareness. These findings support the long-term benefits of building strengths across these five areas. However, despite the promising outcomes associated with PERMA-based interventions, issues of accessibility remain a significant challenge. Many university students still face barriers to participation due to stigma, lack of time, or insufficient availability of mental health resources (25). To address these challenges, the integration of digital tools—such as mobile applications—has been increasingly explored as a scalable and flexible solution (26, 27).

A growing body of research has demonstrated the efficacy of interventions rooted in positive psychology for promoting mental health and well-being among young adults, particularly when delivered through mobile applications. For example, Bendtsen et al. (28) conducted a randomized controlled trial evaluating the impact of a positive psychology–based intervention delivered via a mobile health (mHealth) application. Compared to a control group that received only online mental health information, the intervention group showed significant improvements in positive mental health and reductions in anxiety and depression symptoms at the six-month follow-up. Similarly, Mak et al. (29) compared the effectiveness of basic mindfulness and Health Action Process Approach (HAPA)-enhanced mindfulness programs with a waitlist control group. Both intervention groups demonstrated significant improvements in psychological well-being, which were sustained at the three-month follow-up. However, it´s important to note that none of the reviewed interventions was based on the PERMA model (20). Moreover, a key issue identified in both studies is low adherence rates; Bendtsen et al. (28) reported that participants completed an average of only 2.8 out of 6 planned sessions, highlighting a significant adherence challenge; similarly, Mak et al. (29) noted that just 55% of participants completed the full three-month intervention.

Providing participants with regular check-ins and personalized support via phone could help foster stronger engagement and higher completion rates. Telephone calls offer a more personalized and emotionally engaging form of communication, facilitating deeper connections between users and mental health professionals or support networks. This human interaction may enhance motivation and user retention (30, 31). Furthermore, telephone calls can help bridge the digital divide by offering an alternative to fully digital platforms. For example, Martin et al. (32) found that participants receiving telephone support reported significantly lower psychological distress compared to those in self-administered intervention groups. Beintner and Jacobi (33) showed that consistent telephone prompts significantly increased adherence to an online aftercare program for women with bulimia nervosa. Similarly, Vázquez et al. (34) found that adding multiconference telephone contacts not only improved adherence but also enhanced the outcomes of an app designed to prevent depression in a sample of caregivers. Additionally, a systematic review by Baker et al. (35) supports the effectiveness of telephone-delivered psychosocial interventions in promoting adherence to treatment protocols among individuals with mental health conditions.

To our knowledge, this is the first randomized controlled trial to evaluate a fully PERMA-based psychological intervention delivered via a mobile application in university students, and to directly compare a self-guided app format with a blended format that incorporates synchronous group-based telephone support. By examining not only efficacy but also adherence, satisfaction, and mechanisms of change across PERMA dimensions, this study addresses critical gaps in the digital mental health literature regarding engagement and scalability of positive psychology interventions in higher education contexts. The primary objectives of this randomized controlled trial are to: (a) assess the efficacy of a positive psychology–based psychological intervention grounded in the PERMA model in promoting psychological well-being among university students administered through a smartphone app, with (PPIA + M) and without the addition of telephone multiconference calls (PPIA), compared to a waiting list control group (WLCG); and (b) examine the mediators and moderators of change in psychological well-being. The central hypotheses are that participants in both the PPIA and PPIA+M groups will demonstrate significantly greater improvements in psychological well-being compared to the WLCG at post-treatment and 6-month follow-up, with the PPIA+M group showing more pronounced improvements due to the added telephone support; additionally, it is expected that the change in positive emotion, engagement, relationships, meaning, and accomplishment will mediate the effects of both interventions; and that sociodemographic, academic, and clinical variables, as well as satisfaction with the intervention, will moderate treatment effects. Mediation and moderation analyses are planned as exploratory and hypothesis-generating, aimed at informing future optimization of the intervention.

## Methods and analysis

2

### Design

2.1

A randomized controlled trial (RCT) will be conducted. The present trial protocol follows the CONSORT (36) and SPIRIT (37) statements’ extensions for clinical trials, ensuring the inclusion of all key methodological aspects. Participants will be randomly assigned to one of three groups: (a) an app-based positive psychology–based psychological intervention grounded in the PERMA model (PPIA; experimental group 1); (b) an app-based positive psychology–based psychological intervention grounded in the PERMA model supplemented by telephone multiconference calls (PPIA+M; experimental group 2); or (c) a waiting list control group (WLCG).

The study phases are illustrated in **Figure 1**, which depicts the flow of participants through the trial. Assessments will be conducted at three time points across the three groups: pre-intervention (T1), post-intervention (T2), and follow-up at 6 months (T3). After the baseline assessment, eligible participants will be randomized, and interventions will be administered over five weeks. The post-intervention assessment will be conducted immediately after completion, followed by a follow-up evaluation at 6 months. To ensure participant retention and limit attrition, strategies recommended in clinical research design will be employed. These include clear communication of expectations, structured reminder systems, brief follow-ups in case of missing data, and offering flexible scheduling for phone-based sessions in the PPIA+M group. The intervention app will be designed for ease of use to support consistent engagement (38).

**Figure 1 f1:**
[figure not shown]
SPIRIT figure. Phases of a randomized controlled trial.

### Participants

2.2

#### Recruitment

2.2.1

Participants will be recruited from the student population of the University of Santiago de Compostela (USC). According to the latest available data, USC enrolls approximately 24,095 students across its undergraduate, master’s, and doctoral programs. Recruitment will be conducted using multiple communication channels, including official USC digital platforms, targeted email invitations, printed posters in faculty buildings, and brief in-class announcements during psychology-related courses and student events.

Interested students will be contacted by phone to schedule the initial assessment session (T1) at the University of Santiago de Compostela’s facilities. During this in-person session, the study will be explained in detail, including information regarding the study’s objectives, procedures, potential risks, and expected benefits. Students who agree to participate will be asked to sign a written informed consent form. After obtaining consent, trained evaluators will collect sociodemographic, academic and clinical data and conduct a structured clinical interview (see Section 2.2.7.2.) to determine whether participants meet the eligibility criteria, specifically, the absence of severe psychiatric disorders. Individuals who meet all eligibility criteria will proceed with completing the remaining baseline assessment measures.

#### Eligibility criteria

2.2.2

Inclusion criteria include: (a) being an actively enrolled university student at the University of Santiago de Compostela (USC); and (b) having access to a smartphone with an internet connection. Exclusion criteria include: (a) having a current diagnosis of severe psychiatric disorder, including major depressive disorder with psychotic features, bipolar disorder, schizophrenia, severe cognitive impairment, dissociative disorders, active substance dependence, or active suicidal behaviors; (b) having started psychological or psychopharmacological treatment within the two months prior to the study or participating in another mental health-related study; (c) having insufficient proficiency in Spanish, or presenting sensory, cognitive, or physical impairments that would prevent engagement with the intervention; or (d) planning to move out of Galicia within the next 12 months.

#### Randomization

2.2.3

An independent researcher, who will not be involved in participant recruitment or data collection, will conduct the randomization to maintain allocation concealment. The researcher will generate the random allocation sequence using a computer-generated random number generator. The original randomization sequence will be securely stored by the independent researcher in an inaccessible location, and only the researcher will have access to the sequence. The sequence of assignments will be communicated to the researchers using sealed numbered envelopes, one for each participant, with instructions to open them in numerical order. Due to the nature of the interventions, participants will not be blinded to their treatment allocation.

#### Sample size calculation

2.2.4

The sample size calculation was conducted using G*Power 3.1.9.7, selecting the F-test family and the “ANOVA: Repeated measures, within-between interaction” option. The calculation targeted the omnibus longitudinal group-by-time interaction in a design with three groups and three assessment points. The effect size was entered as Cohen’s *f* = 0.16, which represents a small effect and is approximately comparable to a standardized effect of *d/g* ≈ 0.32 under a simple two-group contrast approximation, based on prior meta-analytic findings that report small but consistent effects of app-based interventions on psychological well-being among university students (26). To account for the two co-primary outcomes, the alpha level was adjusted to α = .025 using a Bonferroni correction. The remaining parameters were statistical power = .95, correlation among repeated measures = .50, and nonsphericity correction *ϵ* = 1. Under these assumptions, the required analytical sample size was 141 participants, corresponding to 47 participants per group, with an actual power of .9509. To allow for an anticipated attrition rate of approximately 20%, the recruitment target was increased to 177 participants, corresponding to 59 participants per group.

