To control the family-wise Type I error rate across the two co-primary outcomes, a Bonferroni-adjusted significance threshold of α = .025 will be applied to the primary confirmatory group-by-time interaction test for each outcome. *Post hoc* pairwise comparisons among the three groups (PPIA vs. WLCG, PPIA+M vs. WLCG, and PPIA+M vs. PPIA) will be conducted using estimated marginal means at post-intervention (T2) and six-month follow-up (T3). Pairwise contrasts will be adjusted using the Bonferroni correction. Effect sizes will be calculated using Cohen’s *d* and interpreted as small (*d* < 0.50), moderate (*d* = 0.50–0.79), or large (*d* ≥ 0.80), following the guidelines proposed by Cohen (63).

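### The 95% power is tied to a standardized effect of about 0.32, but f = 0.16 for this 3×3 interaction means about d = 0.72; power at d = 0.32 is about 24%

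*Protocol article*

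**What the plan says.** Section 2.2.4 (Sample size calculation) names the procedure: "selecting the F-test family and the “ANOVA: Repeated measures, within-between interaction” option". It names the target: "The calculation targeted the omnibus longitudinal group-by-time interaction in a design with three groups and three assessment points". It gives the input, "The effect size was entered as Cohen’s *f* = 0.16", and explains it as a value "which represents a small effect and is approximately comparable to a standardized effect of *d/g* ≈ 0.32 under a simple two-group contrast approximation", citing meta-analytic findings of small effects of app-based interventions on student well-being. For the two co-primary outcomes "the alpha level was adjusted to α = .025 using a Bonferroni correction". With power .95, correlation .50 and epsilon 1, "the required analytical sample size was 141 participants, corresponding to 47 participants per group, with an actual power of .9509". The target is then raised to 177 (59 per group) for about 20% attrition.

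Section 2.2.9 (Statistical analyses) makes the same interaction the confirmatory test for each co-primary outcome at .025. It models T1 as part of the outcome vector. Its scale for reported effects is "interpreted as small (*d* < 0.50), moderate (*d* = 0.50–0.79), or large (*d* ≥ 0.80").

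**The concern.** The value f = 0.16 is half of 0.32, which is the conversion for a one-way comparison of two groups. The test being powered is different. In an interaction, the baseline time point (where randomized groups have no expected difference) and the averaging over nine cells both dilute a given between-group difference. The same d therefore gives a much smaller f.

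The d ≈ 0.32 statement is the only link between the f that was entered and the evidence cited for it. If the link is wrong, the protocol claims 95% power for an effect the trial would probably miss. A non-significant interaction would then be reported from a trial that appears well powered for d ≈ 0.32 when it is not.

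**Working it through.** **Inputs (section 2.2.4).** k = 3 groups, m = 3 times, f = 0.16, alpha = .025, correlation rho = .50, epsilon = 1, N = 141 (177 before attrition).

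**1. Reproduce the stated power.**
- Noncentrality: lambda = f² × N × m / (1 − rho) = 0.0256 × 141 × 3 / 0.5 = 21.66.
- Degrees of freedom: (k − 1)(m − 1) = 4 and (N − k)(m − 1) = 276.
- The noncentral F distribution gives power 0.9510, which agrees with the stated .9509. N = 138 gives 0.9459, so 141 is the smallest balanced size.
- Attrition: 141 / 0.80 = 176.25, rounded up to 177.

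This match fixes the definition of f in use: the root mean square of the nine interaction effects divided by the standard deviation at a single time.

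**2. Convert d to f for this test.** The protocol gives no cell means. Its hypotheses (Introduction, last paragraph) are that both app arms beat the waiting list at T2 and T3. Take equal baselines and an advantage of d in both arms at both later times, in SD units.

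| Arm | Means at T1, T2, T3 | Interaction effects at T1, T2, T3 |
|---|---|---|
| Waiting list | 0, 0, 0 | 4d/9, −2d/9, −2d/9 |
| PPIA | 0, d, d | −2d/9, d/9, d/9 |
| PPIA+M | 0, d, d | −2d/9, d/9, d/9 |

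- Sum of squares: [(16 + 4 + 4) + 2 × (4 + 1 + 1)] d²/81 = 36d²/81.
- Mean over nine cells: 4d²/81, so f = (2/9)d.
- f = 0.16 gives d = 0.16 × 9/2 = 0.72.
- d = 0.32 gives f = 0.32 × 2/9 = 0.0711.

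**3. Power at d = 0.32.**
- N = 141: lambda = 0.0711² × 141 × 6 = 4.28; power 0.238.
- N = 177: lambda = 5.37; power 0.312.
- A simulation of the repeated-measures test (20,000 runs, 47 per group, compound symmetry) gave 0.240 at d = 0.32 and 0.9505 at d = 0.72.
- Smallest d detectable under this pattern with N = 141: 0.59 at 80% power and 0.72 at 95%.
- Analysed N needed at d = 0.32: about 468 for 80% power and about 702 for 95%.

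**4. Vary the pattern.** For sustained effects a (PPIA) and b (PPIA+M), the same algebra gives f = (2/9)√(a² + b² − ab).

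| Pattern, rho = .50 | f | Power, N = 141 | Power, N = 177 |
|---|---|---|---|
| Both arms 0.32, sustained | 0.071 | 0.24 | 0.31 |
| Both arms 0.32 at T2, half at T3 | 0.062 | 0.17 | 0.22 |
| PPIA 0.16, PPIA+M 0.32 | 0.062 | 0.17 | 0.22 |
| PPIA 0.32, PPIA+M 0.48 | 0.094 | 0.45 | 0.57 |
| PPIA 0.32, PPIA+M 0.64 | 0.123 | 0.74 | 0.86 |

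To reach f = 0.16 with PPIA at 0.32, solve 0.32² + b² − 0.32b = 0.72². This gives b = 0.82 for PPIA+M.

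**5. Upper bound.** Over all equal-baseline patterns in which no two groups differ by more than 0.32 at T2 or T3, f is largest when every mean sits at 0 or 0.32, because f is a convex function of the means. Enumerating those patterns gives a maximum f of 0.123 and power 0.74 at N = 141. That maximum needs arms whose effects appear at different times, contrary to the hypotheses.

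**6. Vary the correlation** (both arms 0.32 sustained, N = 141): 0.16 at rho .3, 0.24 at .5, 0.43 at .7 and 0.64 at .8.

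**The case against.** The strongest reply is that the calculation is sound as run. The procedure and every input are named, the power belongs to f = 0.16, and the remark about d is hedged as approximate and as a two-group conversion. The hedge does name the conversion, but that conversion does not fit the test being powered. It is also the only bridge from the cited evidence to the input.

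A second point is that 0.72 and 24% rest on a pattern the protocol does not state, and that the hypotheses expect PPIA+M to do better than PPIA. This stands as a limit on precision: the figures must be given with their pattern, and plausible patterns spread power from 0.17 to 0.74. It does not rescue the claim. The upper end requires an effect of 0.64 in one arm, and even that falls short of 0.95.

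Three smaller points also stand. The word small in section 2.2.4 may refer to Cohen's bands for f, whereas the bands in section 2.2.9 are for d. The article does not say that 0.32 is the pooled estimate in its source, so only the internal mismatch between f and d can be checked. And because the pairwise contrasts are post hoc, stating a detectable difference for each of them is useful but optional.

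**Conclusion.** The concern holds. N = 141 and power .9509 follow correctly from f = 0.16, but that f does not correspond to a standardized difference of about 0.32 in this test. With equal baselines and a sustained, equal advantage in both app arms, it corresponds to d = 0.72, a factor of 0.72 / 0.32 = 2.25. The protocol's own scale for d would call that moderate. Under the same pattern, power at d = 0.32 is 0.24 (0.31 with all 177), and 95% power would need about 702 analysed, roughly five times 141.

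These figures rest on the protocol's alpha .025, correlation .50 and epsilon 1. The specific values change with the pattern and the correlation. The conclusion that 95% power is not available for differences of 0.32 holds for every equal-baseline pattern at the stated correlation. This must be corrected, because it is the stated justification for the sample size.

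**What to change.** In section 2.2.4, delete the statement that f = 0.16 is comparable to d/g ≈ 0.32, and do not carry the label of a small effect over to the d scale. Replace it with text to this effect: 141 analysed participants give 95% power for an interaction f of 0.16; with equal baselines and the same advantage in both app arms at T2 and T3, this is about d = 0.72 (0.59 for 80% power); under that pattern, power at d = 0.32 is about 24%, and it ranges from about 17% to 74% across the other patterns considered (effect halved at T3, or unequal effects in the two arms with PPIA+M up to 0.64). State the assumed pattern beside each figure. Optionally, add the detectable difference for the pairwise contrasts on which the hypotheses rest.

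The cost is a rewording of one section and a less favourable power statement. Recruitment, design and analysis need not change.
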